## 7. Analysis Plan

Five separate studies are addressed, and each will use selected variables from the Core survey, plus module-specific items. For each study, baseline data will first be analysed for the full sample, with a smaller sample entering longitudinal analysis dependent on completing both timepoints of the survey. The analysis plan will evolve depending on our a priori set of research questions, as well as the sample characteristics and final sample size.

*Missing data handling.* Prior to analysis the data set will be cleansed and checked for missing data. Missing data are a critical challenge when dealing with online surveys thus the ENTWINE iCohort survey will employ multiple checkpoints to address this. In the cases where missing data exist, a descriptive analysis of the missing data, as well as a number of hypothesis tests, will be carried out to determine the mechanism of missingness. These tests include Little’s test and Fairclough’s logistic regression method [59,60]. If data are missing completely at random (MCAR), missing values will be subjected to list-wise deletion and complete case analysis will be performed. If data is missing at random (MAR), we will adopt a hot deck imputation for variables with a negligible proportion of missing values (i.e., less than 5%) and multiple imputations by chained equations (MICE) for variables with a larger proportion of missing values [61,62,63,64].

For all analyses, assumptions regarding multicollinearity, singularity, normality, linearity, and homoscedasticity will be tested.

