### 7.1. Modules 1-2-3 Plan Analyses

Descriptive analyses will be performed to establish frequencies, means and standard deviations across key categorical and continuous variables of interest. Bivariate and multivariate analyses, including analysis of variance, *t*-tests and correlations will examine the relationship between caregiver and care recipient characteristics (e.g., age, gender, ethnicity, illness type, type of caregiving relationship, etc.), willingness and motivations to provide care, and key caregiver and care recipient outcomes (e.g., caregiver burden, depression, relationship satisfaction etc.).

Relevant, theoretically informed tests of mediation and moderation will be applied prior to conducting hierarchical multivariate regression analyses to assess the extent of outcome variance explained by the IV set, for example moderating or mediating the effects of: (1) relationship quality, gender, or perceived choice in assuming the caregiver role; (2) willingness to care and relationship quality of the caregiving dyad; (3) interpersonal processes and type of relationship between caregiver and care recipient.

Changes over time in IVs or caregiving outcomes will be analysed in the longitudinal data set using repeated measures tests (*t*-tests, ANOVA, MANOVA).

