## 9. Dissemination

A dissemination strategy has been prepared by the ENTWINE WorkPackage group and our Dissemination and Website Taskforce. This will include dissemination to both academic and non-academic stakeholders in health, public health and social care sectors by means of conference presentations, blogs and multi-media news items on our study website, and preparation of a newsletter providing an executive summary of study findings and their implications.

**Study status**-Baseline recruitment to 31 August 2021; recruitment figures 2736 recruited, 1834 completers (1120 full completion) with follow-up ongoing.
Ireland 14/08/2020–31/05/2021UK 14/08/2020–31/05/2021Poland 14/08/2020–31/05/2021Italy 25/08/2020–31/05/2021Netherlands 16/10/2020–31/05/2021Sweden 23/10/2020–31/05/2021Greece 31/10/2020–31/05/2021Israel 16/02/2021–31/08/2021Germany 17/02/2021–31/08/2021

Participants were invited to take part in the follow up assessment 181 days after the initial baseline invitation. Data collection completed for all countries on 15 December 21; 6 month follow-ups were not offered to participants who completed baseline data after 31 May 2021 due to project funding deadline restrictions.

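### The two-wave change analysis keeps only completers, leaves this unreconciled with the imputation rule, and does not separate participants never offered follow-up from drop-outs

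*Protocol article*

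**What the plan says.** Section 7 (Analysis Plan) has each study analyse baseline data in the full sample first, "with a smaller sample entering longitudinal analysis dependent on completing both timepoints of the survey". Section 7.1, for Modules 1-3, adds: "Changes over time in IVs or caregiving outcomes will be analysed in the longitudinal data set using repeated measures tests", naming t-tests, ANOVA and MANOVA.

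Section 7 also has a missing-data paragraph. It plans a description of the missing data, Little's test and a logistic regression method to judge the mechanism. If data are missing completely at random, "missing values will be subjected to list-wise deletion and complete case analysis will be performed". If they are missing at random, it uses hot deck imputation for variables with under 5% missing and "multiple imputations by chained equations (MICE) for variables with a larger proportion of missing values".

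The study status note in section 9 reports "recruitment figures 2736 recruited, 1834 completers (1120 full completion) with follow-up ongoing", with no split by country. It lists the baseline window for each country and states that "6 month follow-ups were not offered to participants who completed baseline data after 31 May 2021 due to project funding deadline restrictions".

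**The concern.** Three things do not fit together.

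- **Entry rule and imputation rule.** A participant without the second wave never enters the longitudinal set, so imputation within that set cannot bring the participant back. The text does not say which rule prevails.
- **Choice of test.** Paired and repeated-measures tests of this kind use only people with both waves. Baseline records of non-returners, which carry information on who was lost, are not used.
- **Two kinds of absence.** Some participants lack follow-up because they did not return, others because they were never invited. The first kind may depend on burden or wellbeing; the second is set by a calendar date and falls on two countries. The plan does not separate them, although the mechanism tests and any retention figure would be read differently for each.

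At stake are the estimates of mean change over six months and, when countries are pooled, which countries those estimates represent. Differences between countries are among the secondary objectives (section 1.2).

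**Working it through.** **A. Who could not have follow-up**

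The article gives no longitudinal sample size, retention rate or number not offered follow-up, so there is no stated figure to reproduce. The inputs are the dates in section 9. Seven countries closed baseline on 31 May 2021. Israel recruited from 16 February and Germany from 17 February, both to 31 August 2021.

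- Israel: 197 days in the window, inclusive. From 1 June to 31 August is 30 + 31 + 31 = 92 days. 92/197 = 46.7% after the cut-off, 105/197 = 53.3% before it.
- Germany: 196 days. 92/196 = 46.9% after, 104/196 = 53.1% before.
- Other seven countries: 0 days after the cut-off. At most, a survey finished after closing day would be affected.
- Feasibility: "Participants were invited to take part in the follow up assessment 181 days after the initial baseline invitation". 31 May 2021 + 181 days = 28 November 2021, before the close ("Data collection completed for all countries on 15 December 21"). Follow-up was therefore possible for early recruits in both countries.

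Turning days into people needs an accrual pattern, which is not given. Let p be the share of Israeli and German participants with baseline by 31 May, and assume equal baseline numbers in the nine countries. The two countries are then 2/9 = 22.2% of baseline. Their share of the follow-up-eligible sample is 2p/(7 + 2p), and the overall share not offered is 2(1 − p)/9.

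| p (assumed) | Israel + Germany among eligible | Not offered, overall |
|---|---|---|
| 0.75 | 17.6% | 5.6% |
| 0.53 (uniform accrual) | 13.2% | 10.4% |
| 0.25 | 6.7% | 16.7% |

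**B. What completer-only analysis can do to mean change**

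This is an illustration; every input is assumed. Let the baseline score Y1 be standard normal, the true mean change d = 0.20 SD, and the correlation between waves r = 0.6. Completion follows a logistic model in Y1, with the intercept set to give the chosen retention. Since E[change | Y1] = d − (1 − r)·Y1,

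completer-only change = d − (1 − r)·E[Y1 | completed].

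At 55% retention, by numerical integration:

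- Odds ratio 0.8 per SD: E[Y1 | completed] = −0.099; change = 0.20 + 0.4 × 0.099 = 0.24 SD (about 20% too high).
- Odds ratio 0.7: −0.156; 0.20 + 0.4 × 0.156 = 0.26 SD (about 31% too high).
- Odds ratio 0.5: −0.282; 0.20 + 0.4 × 0.282 = 0.31 SD (about 56% too high).

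At 70% retention the three results are 0.23, 0.24 and 0.28 SD. In this setting missingness depends only on the observed baseline, so an estimator that uses all baseline records recovers 0.20 SD.

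The only evidence on engagement in the article is at baseline: 1834/2736 = 67.0% were completers and 1120/2736 = 40.9% gave full completion. This shows that incomplete participation is common, but it is not a follow-up rate.

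**The case against.** The strongest reply is that section 7 already takes missing data seriously, with mechanism tests and multiple imputation, and says that the plan will evolve with the sample. That narrows the point but does not remove it. Entry to the longitudinal set is conditioned on both waves, nothing says that imputation extends to a missing wave, and a promise to evolve names no remedy.

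A second reply is that a funding cut-off set by date does not depend on burden or wellbeing. This stands. Within a country it may be ignorable unless late recruits differ. It costs precision and shifts the country mix; it does not by itself produce the selection shown in part B, which would come from voluntary non-return.

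Third, the bias figures rest on chosen inputs. This also stands: the article gives neither a retention rate nor a link between baseline status and return. In absolute terms the shift at 55% retention and odds ratios of 0.7 to 0.5 is 0.06 to 0.11 SD.

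Two stronger readings are tempting and unsupported. A reader might infer that Israel and Germany lost nearly all their follow-up; yet about 53% of each window precedes the cut-off, and no country counts show a near-total loss. A reader might also infer that the study cannot address determinants over time. Section 7.1 plans hierarchical regressions, and section 8 plans multilevel models with time-lagged associations for the weekly data, so wanting a baseline-adjusted six-month regression as well is a modelling preference, not a defect.

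**Conclusion.** The point holds in a limited form. As written, the two-wave analysis of change in Modules 1-3 drops baseline-only participants, and the imputation rule is not reconciled with that. The resulting bias could be modest or material; its size cannot be known from the article, and 0.26 to 0.31 SD against a true 0.20 SD is an illustration only.

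The administrative cut-off is a separate matter. It is certain in its dates and falls essentially only on Israel and Germany, but its effect in people (about 47% of each) assumes uniform accrual. Its main consequence is lower weight and precision for those two countries in pooled change estimates, which would alter a pooled estimate if change differs by country.

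This should be fixed, but it does not undermine the study. The sample-size case (section 5) does not rest on the two-wave tests, and baseline is analysed first in the full sample.

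**What to change.** 1. Make the main analysis of change a likelihood-based mixed model on all baseline and follow-up records, with time, country, time-by-country and recruitment date. Multiple imputation that explicitly covers the missing second wave, with country and baseline date in the imputation model, is an acceptable alternative.
2. Keep the repeated-measures tests in two-wave completers as a sensitivity analysis.
3. State in section 7 how the two-wave entry rule and the imputation rule relate.
4. Class participants with baseline completed after 31 May 2021 as not offered follow-up. Keep them apart from drop-outs in the missingness tests, leave them out of the retention denominator, and report retention by country among those offered.

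The cost is a change of wording and slightly more analysis work, on data already collected. The main analysis would rely on a missing-at-random assumption, which the data cannot prove. It is weaker than the missing-completely-at-random assumption that completer-only tests of overall mean change generally need.

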## Abstract

Informal caregivers are those who provide unpaid care to a relative or friend with a chronic illness, disability or other long-lasting health or care need. Providing informal care in the context of chronic health conditions presents a significant global challenge. Examination of the determinants of informal caregivers’ behaviour, especially in terms of motivations and willingness to provide/receive care, is crucial to understanding the nature of caregiver and care recipient experiences. A large group of international researchers have co-operated to execute the ENTWINE iCohort-a multinational, transdisciplinary, longitudinal study incorporating intensive methods to examine caregiver experiences in the context of chronic health conditions. The aim of ENTWINE-iCohort is to investigate the broad spectrum of factors, i.e., cultural, personal, geographical, relational, psychological, and economic that may affect motivations, willingness to provide or receive care, among diverse groups of informal caregivers and their care recipients, in different countries that have different care systems. Study questionnaires will be disseminated on-line in nine countries: Germany, Greece, Ireland, Italy, Israel, the Netherlands, Poland, Sweden, and the UK. Cross-sectional and longitudinal multivariate analysis, including intensive longitudinal and dyadic data analysis will be applied to examine the relative contribution of the above factors to caregiver or care recipient wellbeing.

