## 4. Questionnaire Randomisation

Caregivers: the questionnaire for the CG is divided into four modules (Note that the economic, employment and migrant care work sub-components were combined into one module although this addresses the work of 2 ESRs), that is a core module and one module for variables that are specific for each sub-study (1 = cultural aspects; 2 = personality and geographical barriers; 3 = interpersonal processes; 4 = employment and costs including migrant care work). The core module includes personal and demographic information, care context and care task information, willingness to care and wellbeing outcomes (affect, gains, burden). In addition to the core module, participants will randomly receive two other modules (see Figure 1) as programmed within Questback.

This process will reduce the burden for participants and ensures that drop-out and missing values do not centre on specific modules (i.e., if a module is always offered last, this could increase the chance of missing data for this specific module).

Care recipients. The questionnaire for the CR is much shorter and the same for all CRs i.e., there are no modules.

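### Missing-data rule: significance tests that cannot establish MCAR decide when list-wise deletion replaces imputation, and modules withheld by design are not exempted

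*Protocol article*

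**What the plan says.** Section 7 (Analysis Plan, missing data handling) starts with a descriptive look at missing data, after which "a number of hypothesis tests, will be carried out to determine the mechanism of missingness". Little's test and a logistic regression method are named. Two branches follow. For MCAR: "If data are missing completely at random (MCAR), missing values will be subjected to list-wise deletion and complete case analysis will be performed". For MAR: hot deck imputation below 5% missing, and otherwise "multiple imputations by chained equations (MICE) for variables with a larger proportion of missing values". The article gives no significance level for these tests and no rule for conflicting results.

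Three other places bear on this:

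- Section 4 (Questionnaire Randomisation), on caregivers: "In addition to the core module, participants will randomly receive two other modules". There are four such modules. Care recipients all receive one common questionnaire without modules.
- Section 9 (study status): "recruitment figures 2736 recruited, 1834 completers (1120 full completion) with follow-up ongoing". Neither completion term is defined, and caregivers are not separated from care recipients.
- The Abstract lists cultural, personal, geographical, relational, psychological and economic factors and says that multivariate analysis "will be applied to examine the relative contribution of the above factors to caregiver or care recipient wellbeing". Section 7, in contrast, plans five separate studies, each using core variables plus module-specific items.

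**The concern.** A non-significant test of MCAR is not evidence for MCAR; it may only reflect low power. Under this rule a non-rejection leads to the analysis that depends most on MCAR being true, and it withholds the imputation method already in the plan. The gate also gains little: if the data really were MCAR, multiple imputation would remain valid and could still recover information from partial responders.

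Means are most exposed, and they are planned outputs: descriptive means, t-tests and ANOVA in Section 7.1, and estimated care costs in Section 7.2.

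There is a second, separate gap. Modules that a caregiver was never assigned are missing completely at random by construction. Read literally, the MCAR branch sends that missingness to list-wise deletion too, because the rule does not distinguish it from non-response.

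**Working it through.** **1. The plan's own figure.** Section 5: 10 cases × about 30 variables = 300 caregivers per country. This reproduces.

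**2. Precision at stake.** From Section 9: 1834 − 1120 = 714, and 714/1834 = 38.9%. If only full completions were kept, standard errors would grow by up to 1/√(1120/1834) = 1.28, about 28%. This is an upper illustration, because list-wise deletion acts on the variables in each model. For example, with an assumed 2% missing independently on each of 11 variables (10 predictors, as in Section 5, plus the outcome), 0.98^11 = 80% of cases survive.

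**3. Sizes at which the test might be run.** The article does not say whether the tests are run per country, per module or pooled. The sizes tried were:

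- planned per country: 300; planned per country and module: 300/2 = 150
- full completions, assuming an even spread over nine countries and all caregivers: 1120/9 ≈ 124; per module: 124/2 = 62
- pooled completers: 1834

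**4. How often the test detects MAR.** Assumed inputs: outcome y missing in 39%; logit P(missing) = a + b·x for an observed covariate x; corr(x, y) = 0.5; two-sided 5% test of x by missingness. This is a simple stand-in for the named tests. There were 2000 runs per cell (4000 for n = 150).

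| n | rejects, b = 0.2 | b = 0.3 | b = 0.5 |
|---|---|---|---|
| 62 | 11% | 20% | 45% |
| 124 | 17% | 37% | 72% |
| 150 | 22% | 43% | 82% |
| 300 | 37% | 70% | 99% |
| 1834 | 99% | 100% | 100% |

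**5. What follows when the test does not reject.** In the runs where the rule would choose complete cases, the complete-case mean of y is off by about 0.02-0.06 SD. Over all runs, whatever the test result, the shift is about 0.04 SD at b = 0.2, 0.06 at b = 0.3 and 0.09 at b = 0.5. The range 0.02-0.09 SD covers both. The slope of y on x is off by at most about 0.01, as expected when missingness depends only on a covariate in the model.

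**6. Modules withheld by design.** Two of four modules give 6 equally likely pairs (equal allocation assumed).

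| Modules a model needs | Pairs that contain them | Share of caregivers | Of 300 per country |
|---|---|---|---|
| one | 3 of 6 | 50% | 150 |
| two | 1 of 6 | 16.7% | 50 |
| three or four | 0 of 6 | 0% | 0 |

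**The case against.** The strongest reply is that the rule would work where most of the data are. Section 7 analyses baseline data first for the full sample, and at n = 1834 the test almost never misses MAR of the size tried. If drop-out is related to observed variables, the rule would then send the pooled data to imputation, with MICE for variables above the 5% limit. Most of the inferential models are regressions, and their slopes are barely affected in this setting. The simulation inputs are assumptions, and the test simulated is simpler than either named method. All of this stands and limits the size of the problem. It does not rescue the gate, because country-level and module-level analyses are much smaller, means and costs are reported outputs, and the choice of method still rests on a non-rejection.

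A reader might also infer more than the documents support:

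- **That the rule discards 39% of completers.** The completion terms are undefined, caregivers and care recipients are mixed, and deletion depends on the model. The figure is a ceiling under one assumption.
- **That the Abstract's aim cannot be answered because no complete cases exist.** Sections 7 to 7.2 do not plan a model spanning three or more modules. Care recipients have no modules. The core survey, given to every caregiver, already covers several of the listed domains, including religion, income, distance, closeness and relationship satisfaction (Table 1). Section 4 also uses the term missing values in connection with drop-out, so reading unassigned modules into the rule is literal rather than natural.
- **That the absence of an MNAR branch is an error.** A condensed article may leave this to a full analysis plan.

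**Conclusion.** The point holds in limited form. The stated rule can choose complete-case analysis because a test lacked power. At roughly 60 to 300 cases it will often do so under moderate MAR: rejection ranged from 11-45% at n = 62 to 37-99% at n = 300. The possible cost is lost precision, up to about 39% of completers in the extreme case, and a shift in means of about 0.02-0.09 SD. Bias is possible, not certain: under true MCAR only precision is lost, and slopes are little affected under covariate-dependent missingness. These sizes rest on the assumed 39% missing, slopes of 0.2-0.5 and correlation of 0.5.

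On modules, the rule should exempt planned missingness, and the Abstract and Section 7 should be reconciled. The zero-case result applies only to a caregiver model spanning three or more modules.

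**What to change.** 1. Make MICE (or FIML) the primary method for unplanned missingness whatever the tests show, with the outcome, country and core variables in the imputation model.
2. Keep Little's test and the logistic regressions as description, and complete-case analysis as a sensitivity analysis.
3. State that unassigned modules are planned missingness outside the list-wise rule, and run single-module models in the caregivers assigned that module.
4. Say whether a cross-module caregiver model is intended by the Abstract's aim. If so, fit it by FIML or multiple imputation on the pooled sample, where each pair of modules is jointly observed in about one sixth of caregivers.

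The cost is a revised paragraph and modest extra analysis work. MICE is already in the plan and no new data are needed.
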